According to the defined criteria, all undergraduate nursing students at the third year will be recruited as participants. Each academic year, an average of 300 students are enrolled, and for a confidence interval of 95% and a margin of error of 5%, the sample size needed is 169 participants. Also, an a priori 0.05 significance level is defined and a response distribution of 50% is assumed. To prevent potential losses, we've added an additional 15% of the total sample size, thus aiming to recruit 194 students.

All data collection will take place inside the Nursing School, in specifically chosen places, previously tested for the study, and will be performed by two researchers, which will be different from those responsible to analyze data.

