Another variable of interest to characterize the podiatric profile is plantar loading characteristics. As there is no current consensus in the literature for the definition of adequate foot segments, this study will consider the templates of similar studies, which showed good reliability for plantar forces and pressures during barefoot walking in healthy adults (23). Namely, the regions to assess and compare are: lateral heel, medial heel, midfoot, 1st metatarsophalangeal joint (1MPJ), 2nd−5th metatarsophalangeal joint (2–5MPJ), hallux and the lesser toes.

The second primary outcome concerns the change in foot health at 5 months, a subjective evaluation by the participant, and is related to observed clinical parameters, signs and symptoms, namely skin, nails, foot structure, as well as presence and location of the pain. The Portuguese adaptation of the Self-Administered Foot Health Assessment Instrument (S-FHAI), a Likert-type instrument with four dimensions, will be used. It will be applied at month 0 and month 5. The majority of observed foot disorders will be recorded as either present or absent.

The study also includes the following secondary outcomes: (i) Foot Self-Care Knowledge, which is assessed between month 0 and month 5, through a four-dimensional questionnaire, where specific interventions for the promotion and prevention of foot and ankle disorders are evaluated; and (ii) Students' perceptions about the influence of foot health in their quality of life. It is evaluated through focus groups after exposure time (month 5).

Regarding potential effect modifiers and confounders, we expect that different nursing activities and ward typology (e.g., surgical units, intensive care) might produce diverse baropodometric patterns.

The primary and secondary outcomes, respective instruments for evaluation and timeframes for assessment are summarized in Table 2.

**Table 2 T2:** Primary and secondary outcomes assessment.

			**Assessment**	**Timeframe**		
				**Month 0**	**Month 3**	**Month 5**
**Primary Outcomes**	Change in Podiatric Profile at 5 months^*^	Kinematic variables	EMED® software	x		x
		Kenetic variables		x		x
		Foot posture	MAI analysis	x		x
		Foot function	CPEI analysis	x		x
	Change in Foot Health at 5 months	Skin health	Portuguese adaptation of the self-administered foot health assessment instrument [S-FHAI; (24)].	x		x
		Nail health		x		x
		Foot structure		x		x
		Foot pain		x		x

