### Statistical Analysis

The primary outcomes and the Foot Self-Care Knowledge (secondary outcome) will be analyzed using SPSS Statistics v25, namely with descriptive statistics (average; standard deviation; medians) with an *a priori* significance value of *p* < 0.05.

After verifying the type of distribution of the sample, using the Kolmogorov-Smirnov (KS) with Liliefors correction (suitable for samples with more than 30 subjects) (30), either the independent samples *t*-test (normal distribution) or the Mann-Whitney (test non-normal distribution) will be used to compare changes in outcomes before and after the exposure.

To relate variables of interest, namely podiatric profile variables and specific foot-health parameters, a Multiple Linear Regression will be computed and multivariate analysis of variance with repeated measures to detect significant interactions between variables.

To control confounding effects, we'll perform a stratification of variables, and evaluate the exposure-outcome association, also using Mantel-Haenszel (M-H) estimator for an adjusted result. Additionally, the Analysis of Covariance (ANCOVA) will be computed to assess the effect of certain factors on the outcome variables.

The secondary outcome, related to the students' perceptions, will be analyzed using ATLAS.ti v7 software, based on the content analysis as defined by Bardin (31). The different phases of analysis are: (i) pre-analysis; (ii) exploration of the material; and (iii) treatment of results, inference and interpretation. The categorical organization of the content will be performed *a posteriori*, through the following codification steps: (i) cutting—choice of units; (ii) enumeration—choice of counting rules; and (iii) classification and aggregation of chosen categories and units.

Potential missing data will be handled using marginal mean imputation, this is, computing the mean of the missing value, *X*, using the non-missing values and use it to impute missing values of *X*.

Regarding loss to follow-up, all data belonging to participants that choose to opt-out or are lost during the study, will be erased from storage, as explained in the informed consent document.

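### Filling every gap with the marginal mean understates the variance of the imputed variable, distorts the planned regressions and, read literally, puts fractions into present/absent items

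*Protocol article*

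**What the plan says.** The Statistical Analysis section names one method: "Potential missing data will be handled using marginal mean imputation". It explains this as a mean computed "using the non-missing values and use it to impute missing values of" that variable. No variable type is excluded, no predictor of the missing value is used, and no sensitivity analysis accompanies the rule.

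The same section lists the analyses that would run on the filled-in data:
- an independent-samples t-test or Mann-Whitney test, which "will be used to compare changes in outcomes before and after the exposure";
- a regression linking podiatric profile to foot-health parameters ("a Multiple Linear Regression will be computed");
- repeated-measures MANOVA and ANCOVA;
- stratification, "also using Mantel-Haenszel (M-H) estimator for an adjusted result".

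Two other statements set the reach of the rule. For the second primary outcome, the section on exposures, outcomes and confounders says: "The majority of observed foot disorders will be recorded as either present or absent". On losses, Statistical Analysis says that "all data belonging to participants that choose to opt-out or are lost during the study, will be erased from storage".

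**The concern.** An imputed mean is a constant that is then analysed as if it had been measured. It adds to the sample size but adds no spread and no covariance with any other variable. Three consequences matter here.

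- Relating podiatric profile to signs and symptoms is a stated aim, and the regression that serves it works on covariances that the rule dilutes.
- Both primary outcomes are changes between month 0 and month 5. A student with a gap at month 5 is given the group mean minus the student's own baseline, which discards the within-person correlation that a before-and-after design relies on.
- The mean of a 0/1 item is a fraction, which is neither present nor absent.

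The method is stated as the plan, so this is not a detail left to a fuller document.

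**Working it through.** **Inputs.** From the article: the imputation rule, the planned analyses, the present/absent recording, erasure of lost participants' data, and n = 169. Assumed, because the article gives no figure: the fraction m missing among retained students, the month 0/month 5 correlation ρ, and the mechanism. Outcomes are in units of one visit's SD.

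**The plan's own figure.** The sample size reproduces: 1.96² × 0.25 / 0.05² = 384.16; 384.16 / (1 + 383.16/300) = 168.7, rounded up to 169; 169 × 1.15 = 194.35, about 194. It does not depend on the imputation rule. The 15% in it is an allowance for losses, not a rate of gaps in retained students.

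**1. Variance and SE of an imputed variable, missing completely at random.** The variance falls to (1 − m) of its true value. The naive SE of the mean is √((1 − m)σ²/n) and the correct SE is σ/√(n(1 − m)), so the ratio is 1 − m: 0.95, 0.90 and 0.85 at 5%, 10% and 15% missing. A nominal 95% interval for that mean covers 2Φ(1.96(1 − m)) − 1, which is about 94%, 92% and 90%. Simulation at n = 169 with 15% missing gave a naive SE of 0.071 against an empirical 0.081 to 0.085.

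**2. Regression with the outcome imputed.** The covariance with the predictor falls to (1 − m) of its true value and the predictor's variance is unchanged, so the slope falls to 0.95, 0.90 and 0.85 of truth. Simulation agreed. Correlations fall by √(1 − m), to about 0.97, 0.95 and 0.92.

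**3. Regression with one of two predictors imputed.** Take true coefficients of 0.50 and 0.50 and a predictor correlation of 0.6.
- The normal equations are b1 + 0.6·b2 = 0.8 and 0.6(1 − m)·b1 + b2 = 0.8.
- They give b2 = (0.8 − 0.48(1 − m)) / (1 − 0.36(1 − m)).
- At m = 0.10, b2 = 0.368/0.676 = 0.54 and b1 = 0.8 − 0.6 × 0.544 = 0.47.
- At m = 0.15, b2 = 0.392/0.694 = 0.56 and b1 = 0.46.

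The imputed predictor loses weight and the other gains it. Simulation gave 0.47 and 0.55, then 0.46 and 0.57.

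**4. Present/absent items.** With an assumed prevalence of 30%, a missing item becomes 0.30, which is not a whole count for a 2×2 stratum.

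**5. Mean change, month 5 missing.** If gaps are completely random, the bias is zero. If the probability of a gap depends on baseline x as Φ(a + x), with overall fraction m, the bias is −ρ·φ(Φ⁻¹(m)) / (√2(1 − m)). At ρ = 0.8:
- 2% missing: 0.8 × 0.0484 / (1.414 × 0.98) = 0.028, a bias of about −0.03 SD;
- 5% missing: 0.8 × 0.1031 / (1.414 × 0.95) = 0.061, a bias of about −0.06 SD.

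The sign reverses if low-baseline students are the ones with gaps.

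**6. Variance of the change score, completely random gaps.** The ratio to truth is 1 − m + m / (2(1 − ρ)). It equals 1 at ρ = 0.5 and exceeds 1 above that. At ρ = 0.8 it is 0.90 + 0.10/0.4 = 1.15 at 10% missing and 0.85 + 0.15/0.4 = 1.23 at 15%. Here the variance is overstated.

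**The case against.** The strongest reply is that the rule will have little to act on. Lost participants' data are erased, so the obvious source of month-5 gaps never reaches imputation. Under Study Layout, invalid walking trials are repeated until three are valid per foot, and the foot-health questionnaire is completed in the same session. This stands: nothing in the article supports 10% or 15% missing among retained students.

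A reader might also infer three stronger things, and none is supported.

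- *That false-positive rates reach 45% to 71%.* Those figures arise in an assumed scenario (n = 169, ρ = 0.8, 10% to 15% missing, probit slope 1 on baseline) for a paired test. The article plans an independent-samples test. In the same scenario that test rejects about 6% of the time at 10% missing and about 24% to 25% at 15%, and under 1% when gaps are completely random. Whether an independent-samples test suits paired data is a separate matter.
- *That variance is understated everywhere.* This holds for the imputed variable. The change-score variance is overstated once ρ exceeds 0.5.
- *That change is always biased and every slope attenuated.* Mean change is unbiased under completely random gaps. A non-imputed predictor's coefficient can rise, and with a single predictor imputed the slope equals the complete-case slope.

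It can also be said that the article does not expressly apply the mean to binary items and calls the foot-health instrument Likert-type. That is fair. The fraction problem follows from wording that carries no restriction, and a restriction would remove it.

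**Conclusion.** The concern holds in a limited form and should be fixed. As written, the rule treats imputed constants as data. For any imputed variable, completely random gaps are enough to understate its variance and the SE of its mean by about the missing fraction. Under the same mechanism, slopes on an imputed outcome are attenuated by that fraction and multiple-regression coefficients are distorted when a predictor is imputed. Read literally, the rule also gives unusable values for present/absent items. Bias in mean change needs more: gaps that relate to baseline, with −0.03 SD at 2% and −0.06 SD at 5% missing as illustrations.

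All sizes rest on assumed missing fractions, correlations and mechanisms, and apply only to retained participants. If gaps are few, the practical effect is small. The case for change is that the rule is inferior to available methods and cheap to replace, not that the article shows large damage.

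**What to change.** Delete marginal mean imputation. For retained participants:

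- Analyse all observed values with a linear mixed model with visit as a fixed effect. For present/absent items use GEE or a mixed logistic model.
- Where the regressions need completed data, use multiple imputation that includes the other-visit value, ward type and the other outcome variables, with a logistic imputation model for present/absent items.
- Add a complete-pair analysis as a sensitivity analysis only. In the ρ = 0.8 scenario with 10% to 15% missing it is itself biased by 0.03 to 0.04 SD, and at ρ = 0.5 it is about as biased as mean imputation.

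Because lost participants' data are erased, none of these methods can recover information from them, and the text should say so. The change needs no extra participants, visits or measurements. It costs a revised paragraph and slightly more analysis work.

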## Discussion

We have described a protocol for a prospective observational cohort study, that aims to understand the influence of prolonged standing and walking positions on nursing students' foot health. This study will also explore the potential relationship between nursing students' podiatric profile and reported signs and symptoms.

Nursing practice is physically demanding, causing high loading forces, namely to the lower extremities. Additionally, common factors for increased risk for the development of foot/ankle disorders are footwear, constant standing and neglected foot care (6).

Currently, the study of injuries has been the subject of several studies, and some (31, 32) report that further investigations should be carried out into the circumstances and factors that cause problems at the level of foot/ankle region in this population.

Although several studies identify this problem, few describe in detail the causes of pain and discomfort. On the other hand, the podiatry evaluations conducted are poor (31), which limits a more detailed knowledge of the phenomenon under study. Moreover, and although some researchers suggest some solutions, namely the development of ergonomic and personalized footwear (33–35), there seems to be no adequate interventions to improve foot health in nursing students (4, 13).

Therefore, this study has the potential to comprehensively map significant foot/ankle changes caused by prolonged walking or standing positions, experienced by nursing students in clinical settings. Such data will be essential to establish a potential relationship between those factors. The conclusions will lead to a better understanding of the phenomena, thus allowing for better prevention. Additionally, the conclusions will lead to a better understanding of the phenomena, thus allowing for a better prevention, particularly through the development of guidelines and preventive tools.

Some limitations of the study are related to the convenience sample, which is recruited from a Nursing School in Portugal, reducing the external validity of the study. On the other hand, the follow-up time of 5 months, may be insufficient to elicit important signs and symptoms.

## Ethics Statement

The study was approved by the Ethical Committee of the Health Sciences Research Unit: Nursing (UICISA: E), of the Nursing School of Coimbra (ESEnfC), with the approval code no. P799_07_2021. The study was also recorded in ClinicalTrials.gov on the number NCT05197166. Participants will first be addressed in a project presentation session, where informed consent will be provided for their analysis and signature.

